## Abstract

**Background:**

The prevention of type 2 diabetes is a globally recognised health care priority, but there is a lack of rigorous research investigating optimal methods of translating diabetes prevention programmes, based on the promotion of a healthy lifestyle, into routine primary care. The aim of the study is to establish whether a pragmatic structured education programme targeting lifestyle and behaviour change in conjunction with motivational maintenance via the telephone can reduce the incidence of type 2 diabetes in people with impaired glucose regulation (a composite of impaired glucose tolerance and/or impaired fasting glucose) identified through a validated risk score screening programme in primary care.

**Design:**

Cluster randomised controlled trial undertaken at the level of primary care practices. Follow-up will be conducted at 12, 24 and 36 months. The primary outcome is the incidence of type 2 diabetes. Secondary outcomes include changes in HbA1c, blood glucose levels, cardiovascular risk, the presence of the Metabolic Syndrome and the cost-effectiveness of the intervention.

**Methods:**

The study consists of screening and intervention phases within 44 general practices coordinated from a single academic research centre. Those at high risk of impaired glucose regulation or type 2 diabetes are identified using a risk score and invited for screening using a 75 g-oral glucose tolerance test. Those with screen detected impaired glucose regulation will be invited to take part in the trial. Practices will be randomised to standard care or the intensive arm. Participants from intensive arm practices will receive a structured education programme with motivational maintenance via the telephone and annual refresher sessions. The study will run from 2009–2014.

**Discussion:**

This study will provide new evidence surrounding the long-term effectiveness of a diabetes prevention programme conducted within routine primary care in the United Kingdom.

**Trial registration:**

Clinicaltrials.gov NCT00677937

## Background

Type 2 diabetes mellitus (T2DM) represents one of the greatest global public health challenges in the 21^st^ century [1]. High glucose levels are currently recognised as the third leading cause of mortality globally and treatment accounts for 7-14% of total health care spending across all global regions [2,3]. International and national health care organisations have responded to this urgent health care need by focusing on recommendations and policy aimed at prevention. In the United Kingdom, this has taken the form of the NHS Health Checks programme which is aimed at screening all individuals between 40 to 75 years of age for vascular and metabolic disease risk and then treating high risk individuals accordingly [4]. Preventing T2DM is one of the fundamental aims of this programme. However in the UK, as in many other parts of the globe, translational research has lagged behind policy change and there has been a lack of diabetes prevention programmes specifically developed for, and evaluated in, routine health care settings.

Although large and well conducted randomised controlled trials have consistently shown that lifestyle interventions can reduce the risk of progressing to T2DM by 30 to 60% in those with impaired glucose tolerance (IGT), an intermediary high risk state between normal glucose regulation and T2DM [5], there is no data from the UK. There also remain important gaps in the evidence when it comes to translating diabetes prevention research into practice [6]. The majority of tested lifestyle intervention studies have used intensive behaviour change strategies relying on multiple and lengthy one-to-one patient contacts which would be unsustainable in a routine health care setting due to cost and infrastructure limitations. Several countries have responded to this limitation by developing, evaluating and implementing diabetes prevention programmes that have been tailored to the needs of their specific health care settings [7]. Although these programmes have varied in context and scope, they have consistently settled on utilising group-based educational programmes as the primary vehicle for promoting behaviour change [8-11]. A recent pilot study in the UK added to these international developments by demonstrating that a 3-hour structured education programme was highly effective at promoting behaviour change, improving glucose regulation and reducing the risk of T2DM in those with IGT at 12 months which were sustained at 24 months [12,13]. In the UK, structured education is already a widely advocated method of promoting self-management strategies and a healthy lifestyle in individuals with T2DM and forms an essential component in integrated diabetes management pathways nationally [14,15]. For example, the established DESMOND programme for individuals with T2DM is delivered nationally and internationally as part of routine care and has been shown to be highly cost-effective [16]. Given the current focus on prevention, there is considerable potential and interest for extending the educator training and quality assurance infrastructure that have accompanied programmes focused on diagnosed chronic disease to the prevention of T2DM. However, this approach needs to be rigorously evaluated when conducted in a primary health care setting.

Another potential limitation when considering the translation of diabetes prevention programmes into “real world” settings is the disconnection between the population used in traditional diabetes prevention programmes and routine clinical practice. Diabetes preventions programmes have typically included individuals on the basis of an oral glucose tolerance test (OGTT) and the presence of IGT [5]. However, such tests may not be appropriate for universal screening given they are costly, time consuming and inconvenient [17]. Both patients and health care professionals have reported that the OGTT is a barrier to attending screening [18]. Additionally studies have shown a low up-take to screening with an OGTT [19] and participation in targeted screening programmes is generally higher [20,21]. Therefore pragmatic alternatives are required. Current international consensus favours a stepped approach whereby high risk individuals are identified using risk score technology which is followed by a blood test to confirm high risk status and rule out the presence of T2DM [22]. Those confirmed with a high risk status can then be referred to a prevention programme. However, the effectiveness and cost-effectiveness of combining a stepped screening strategy with a behaviour intervention has not been evaluated in a usual health care setting; this greatly limits the ability of health care commissioners to make informed decisions when allocating resources. This study will address these points by screening those deemed at high risk of T2DM using a risk score and recruiting those found to have Impaired Glucose Regulation (IGR, a composite of IGT and/or impaired fasting glucose (IFG)) into a prevention programme, and then by formally assessing the cost-effectiveness of this strategy.

## Aim

The aim of the study is to establish whether a pragmatic structured education programme targeting lifestyle and behaviour change in conjunction with motivational maintenance via the telephone is cost-effective and can reduce T2DM incidence in people with IGR identified through a two stage screening programme in primary care.

## Methods/Design

The study consists of two phases. A screening phase where people at risk of IGR/T2DM are identified using a validated risk tool and secondly an intervention phase where those identified with IGR will be recruited in to a T2DM prevention cluster randomised trial.

### Phase 1: the screening phase

#### Identification of those at high risk of having IGR/T2DM

All participating GP practices will receive a Practice Pack giving them general information and contact numbers for the study. All practices will have an induction visit from the project lead and research assistant who will provide training and support.

An automated risk score will be used to identify those at high risk of IGR/T2DM using data routinely stored on individual GP practice computer databases. Various risk scores have been developed and validated for identifying T2DM [23]. Scores available to date have not been validated for the UK multiethnic population and do not additionally pick up those with IGR. Therefore we will use a score developed using data from a previous screening study carried out in Leicester [24]. This score has been amended to take into account ethnicity using the percentage of South Asians within the practice as a proxy for individual ethnicity.

Before the risk tool is applied to a practice database the quality of the data completion is assessed. If the quality level of Body Mass Index (BMI) data recorded is less than 40% practices will be asked to increase this before the risk tool can be used. The score will be calculated for all members of a participating practice. The practice list will then be ranked by risk score with those with the highest scores having the highest risk. The top 10% of patients with the highest score will be invited initially for screening. This 10% limit can be increased to generate further invitations and increase inclusion in the study if required. Where the top 10% of the risk score identifies fewer than 500, all patients within the top 10% will be invited. Where the number of eligible patients identified in the top 10% is greater than 500, the first 500 patients within the top 10% will be invited. If the response rate to initial invitations is insufficient a second mailing of invitations will be conducted. A computer programme will be written to automate the process and produce an excel spreadsheet listing risk scores in descending order.

The invitation will include a patient information sheet and a reply sheet, so patients can register their interest in taking part in the study. A self addressed envelope will be provided for returning of slips. Patients will also be given the number of a dedicated phone line to contact if they are interested and/or require further information. Written informed consent will be taken from all participants and participants will be able to withdraw from the study at any time.

#### Inclusion criteria

Patients are invited for screening if they fulfill the following criteria:

· High risk according to a validated practice risk tool

· Aged 40 to 75 years if English speaking European or 25–75 years if South Asian

#### Exclusion criteria

Patients are excluded from the study if they are/have:

· Unable to give informed consent

· Pregnant or lactating

· Established diabetes

· Terminal illness

· Require an interpreter for language other than South Asian

#### Baseline screening visit

Participants will be asked to fast for 8 hours prior to attending the screening appointment and to bring a list of prescribed medications with them. Before beginning the overnight fast participants are asked to consume their regular evening meal and take any medication as normal. All participants receive a standard 75 g OGTT following informed consent being taken. Those patients who do not wish to have an OGTT will be discontinued from the study and return to their GP for routine care. Plasma samples are obtained immediately before (fasting plasma glucose) and 120 minutes after the glucose challenge (two hours post challenge glucose) along with fasting samples for serum urea and electrolytes, liver function, lipids (total cholesterol, LDL-cholesterol, HDL-cholesterol, triglycerides), and HbA1c. A number of biomarkers will also be measured including: tumor necrosis factor-α, interleukin-6, leptin, adiponectin, resistin, hs-CRP, and PAI-1. Insulin resistance will be measured using HOMA-IR. Levels of vitamin D and C will also be measured.

Results will be relayed via written correspondence and copied to participant and general practitioner. All biochemical measurements will be performed in-house at the University Hospitals of Leicester NHS Trust, UK. Glucose samples will be taken in fluoride oxalate test tubes and placed immediately in a portable 4 litre 4°C refrigerator. HbA1c% will be analysed by a DCCT aligned Biorad Variant HPLC II system (Bio-Rad laboratories, Hemel Hempstead, UK). The imprecision coefficient of variation of this machinery is <0.1%, and the reference intervals fit with national recommendations valid for carriers of variant Hb S, C and Q. Samples will be processed within a maximum of two hours, using an Abbott Aeroset clinical chemistry analyser (Abbott laboratories, Maidenhead, UK), which employs the hexokinase enzymatic method. This machinery has an imprecision coefficient of variation of 1.61%. Serum total cholesterol, HDL-cholesterol, LDL-cholesterol and triglycerides will be measured by means of enzymatic techniques (Dade Behring Dimension analyser, Newark, USA). Plasma creatinine will be analysed with kinetic colorimetric methods. Plasma levels of urea and electrolytes, bilirubin, alanine aminotransferase, alkaline phosphatase and thyroid stimulating hormone will be analysed by means of the Dade Behring Dimension analyser.

Participants will be categorised according to World Health Organisation (WHO) criteria [25]. Diabetes will be defined as a fasting blood glucose of greater or equal to 7 mmoll^-1^ and/or 2 hour plasma glucose of greater than or equal to 11.1 mmoll^-1^. Anyone who has an OGTT result in the diabetes range will be recalled as soon as possible for a second, confirmatory test for diabetes. Those found to have diabetes at baseline will discontinue the study and receive standard diabetes care from their general practitioner; those found to have diabetes during follow up will remain in the study (but not receive OGTTs, further follow up education or support phone calls) and again be referred to their general practitioner for their diabetes care. In this study IGR or ‘pre-diabetes’ will be defined as IFG and/or IGT. IFG will be defined as a fasting blood glucose concentration of between 6.1 and 6.9 mmoll^-1^ inclusive and IGT as a 2-hour blood glucose concentration of between 7.8 and 11 mmoll^-1^ inclusive.

Anthropometric measurements will be performed by trained staff using standard operating procedures. BMI will be calculated after the body weight (kg) and height (m) are measured, weight to be measured in light clothing without shoes to the nearest 0.5 kg. Waist circumference will be measured with a soft tape on standing participants, mid-way between the lowest rib and iliac crest to the nearest 0.1 cm. Hip circumference will be measured over the widest part of the gluteal region, and the waist-to-hip ratio calculated. Three blood pressure recordings will be obtained from the right arm of the patient in a sitting position after 3 minutes of rest, at 1 minute intervals, and then the mean value will be calculated of the second and third reading discounting the first. Seven day step count will be assessed by giving all participants a sealed piezoelectric pedometer (NL-800). Participants will be asked to wear the pedometer, fitted to their trunks (placed on right anterior axillary line) for seven consecutive days during waking hours. Participants will be provided with a stamped addressed envelope to return the pedometers to the study co-ordinators.

A trained nurse will collect data on previous and current medical history, medication and family history using a standard form. Self completed questionnaires will be used to assess smoking status, alcohol consumption, occupation, sleep habits and ethnicity. Social deprivation will be determined by assigning an Index of Multiple Deprivation (IMD) score to participant postcodes [26]. IMD scores are publicly available continuous measures of compound social and material deprivation which are calculated using a variety of data including current income, employment, health, education, and housing.

The following validated questionnaires will also be collected

· The Dietary Instrument for Nutrition Education or DINE food frequency questionnaire will be used to assess dietary fat and fibre intake [27]

· The Health State Descriptive System to assess quality of life, known as 15D [28]

· The Hospital Anxiety and Depression HADS – validated for depression and anxiety relating to diagnosis of condition and the care provided thereafter [29]

· The Brief Illness Perception Questionnaire or BIPQ designed to quickly assess cognitive and emotional representations of illness [30]

· The International Physical Activity Questionnaire (short form) (IPAQ) to obtain internationally comparable data on health–related physical activity [31]

Patients will also self-report on two questions concerning sleeping pattern (how many hours sleep did you get last night? And on average, how many hours do you sleep in 24 hours) [32].

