**Figure 1 F1:**
[figure not shown]
Study participation.

**Table 1 T1:** Clinical assessment and measures

Measurements	Time points				
	Baseline/Screening	Trial 6 m	Trial 12 m	Trial 24 m	Trial 36 m
	Clinical Assessment					
Medical History	X		X	X	X	
Medication History	X		X	X	X	
Physical Exam	X		X	X	X	
Cardiovascular Risk Score	X	X	X	X	X	
Presence of Metabolic Syndrome	X	X	X	X	X	
	Anthropometric					
3 x Blood Pressure	X	X	X	X	X	
Height	X				X	
Weight	X	X	X	X	X	
Waist Circumference	X	X	X	X	X	
Blood Tests						
Oral Glucose Tolerance Test	X		X	X	X	
HbA1c	X	X	X	X	X	
Lipids	X	X	X	X	X	
Urea & Electrolytes	X		X	X	X	
Liver Function Tests	X		X	X	X	
	Questionnaires & Lifestyle Measures					
IPAQ – SF [31]	X	X	X	X	X	
DINE [27]	X	X	X	X	X	
BIPQ [30]	X	X	X	X	X	
HADS [29]	X	X	X	X	X	
15D [28]	X	X	X	X	X	
	Health care resource use					X
EQ-5D [38]					X	
Sleep questions	X	X	X	X	X	
7 Day Step Count	X	X	X	X	X	
Urine Sample	X		X	X	X	

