#### Exclusion criteria

Patients are excluded from the trial if they are:

· Diagnosis of diabetes at screening/baseline (if diagnosed during the study participants are invited to continue without the 120 glucose sample or further intervention activities)

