#### Endpoints and outcomes

The primary outcome aims to show the reduction in the incidence of T2DM at 36 months in people with screen-detected IGR. Secondary outcomes are reductions in HBA1c, blood glucose levels fasting and post glucose load, cardiovascular risk as calculated by the Framingham risk calculator [48] and the presence of Metabolic Syndrome as defined by NCEP ATP III [49], increasing seven day step count and cost-effectiveness of the intervention.

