#### Data analysis

At major time points and at study completion the findings will be reported according to the internationally recognised CONSORT statement for the reporting of cluster randomised control trials [54]. Data will be analysed on an intention to treat basis (ITT). Data will be analysed using STATA v10, and all analysis will take into account the clustering by GP practice. Survival curves would be calculated to estimate the cumulative incidence of diabetes. The difference in incidence of T2DM in the groups is tested using the two-sided log-rank test adjusted for cluster. Differences in secondary outcomes between the groups will be assessed using either linear for continuous outcomes or logistic for categorical outcomes regression with treatment group as the independent variable.

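### The 2-hour glucose sample stops at diagnosis, so a 36-month regression of post-load glucose on treatment group is selected on the primary outcome and is not intention to treat

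*Protocol article*

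**What the plan says.** The protocol article fixes four things that bear on this point.

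- **Measurement.** Under Baseline screening visit, "those found to have diabetes during follow up will remain in the study (but not receive OGTTs". The Phase 2 Exclusion criteria repeat the rule: "if diagnosed during the study participants are invited to continue without the 120 glucose sample or further intervention activities". The two passages agree. Baseline screening visit also requires a second, confirmatory test for a result in the diabetes range, and refers diagnosed participants to their GP for diabetes care.
- **Outcome.** Endpoints and outcomes lists "blood glucose levels fasting and post glucose load" among the secondary outcomes.
- **Analysis.** Data analysis sets an intention-to-treat basis for the data, asks for clustering by practice to be taken into account, and states: "Differences in secondary outcomes between the groups will be assessed using either linear for continuous outcomes or logistic for categorical outcomes regression". Treatment group is the only independent variable named.
- **Schedule.** Table 1 places the "Oral Glucose Tolerance Test" at baseline, 12, 24 and 36 months and notes no exception for diagnosed participants.

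**The concern.** These statements do not fit together for 2-hour glucose. Anyone diagnosed at the 12- or 24-month visit has no 36-month value, by design. One of the two criteria for diagnosis is "2 hour plasma glucose of greater than or equal to 11.1" mmol/l, so the people who drop out of this outcome tend to be those with the highest values. If the intervention works, more of them are in the control arm. A regression of the 36-month values on treatment group then compares subsets chosen by the trial's primary outcome, and randomisation no longer protects the comparison.

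This differs from ordinary dropout, because the protocol itself creates the gap and ties it to the outcome. Readers will also look at this outcome closely: the Power calculation section uses a 1.3 mmol/l fall in 2-hour glucose in an earlier trial to support the assumed effect.

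**Working it through.** **1. Planning rates.** From Power calculation: control conversion 35% at three years and a 40% relative reduction, so 0.35 × (1 − 0.40) = 0.21 in the intensive arm. To confirm this reading I reproduced the stated sample size. Two proportions, 0.35 versus 0.21, two-sided 5%, 80% power: 161 per arm. Design effect 1 + (17 − 1) × 0.05 = 1.8, so 161 × 1.8 = 289.8. Allowing for 20% dropout, 289.8 / 0.80 = 362.25, or 363. Then 363 / 17 = 21.4, rounded up to 22 practices, and 22 × 17 = 374 per group, as stated. The sample size is unaffected by this point.

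**2. Who lacks a 36-month value.** The protocol gives only the three-year rate, so I assume a constant hazard: proportion diagnosed by year t = 1 − (1 − p)^(t/3).

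| | Control (p = 0.35) | Intensive (p = 0.21) |
|---|---|---|
| Diagnosed by 24 months, no 36-month value | 1 − 0.65^(2/3) = 25.0% | 1 − 0.79^(2/3) = 14.5% |
| First diagnosed at 36 months, value available | 0.7504 − 0.65 = 10.0% | 0.8546 − 0.79 = 6.5% |
| Of 374 enrolled, no value for this reason | about 93 | about 54 |

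This comes before the 20% dropout. The shares depend on timing: were every conversion found by 24 months they would be 35% and 21%; the later conversions occur, the smaller they become.

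**3. What the omission does to the arm difference.** Let g be the mean 36-month 2-hour glucose of those not measured minus that of those measured, taken as equal in both arms. Each arm's full mean is its observed mean plus share × g. The control-minus-intensive difference in the observed data is therefore too small by g × (0.2496 − 0.1454) = 0.104 g. For g = 1, 2 and 3 mmol/l that is 0.10, 0.21 and 0.31 mmol/l. For g = 0 there is no bias, and for negative g the bias reverses. The documents do not give g.

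**4. Simulations with no effect of care after diagnosis.** All glucose parameters (mmol/l) are assumptions. Measurement stops on confirmed 2-hour values only.

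| Assumptions | Share of the true 36-month difference recovered from available values |
|---|---|
| Between-person SD 1.0–1.5, within-person SD 1.0–1.5, mean drift 0.1–0.3 a year, conversion set to 35% and 21% | True 0.74–0.95 appears as 0.40–0.60 (0.40/0.74 = 54% to 0.60/0.95 = 63%); true 1.3 appears as 0.76–0.85 (58–65%) |
| Baseline mean 8.6, SD 1.5, within-person SD 0.7–1.0 | 0.66/1.01 = 65%; 0.35/0.51 = 69%; 0.70/1.00 = 70%; 0.93/1.30 = 72% |
| Baseline mean 8.6, between-person SD 1.0–1.5, within-person SD 0.7–1.5, conversion set to 35% and 21% | 63–83% |

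**5. Simulations with care after diagnosis.** Baseline mean 8.6, between-person SD 1.5, within-person SD 0.85, assumed pre-diagnosis effect 0.5 mmol/l. The target is now 36-month glucose as it actually is, including the effect of care.

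| Assumed fall in 2-hour glucose after diagnosis | Diagnosis on 2-hour values only | Some diagnoses on fasting glucose (assumed 8% yearly hazard in control) |
|---|---|---|
| 0 | 76% | 83% |
| 1 mmol/l | 92% | 105% |
| 2 mmol/l | 116% | 142% |

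In a separate check, a fall of roughly 1 to 2.3 mmol/l cancelled the bias.

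**6. Alternatives, in the second row of step 4.** Carrying the diagnostic value forward recovered 80–85%. Sequential regression on all earlier OGTT values recovered 92–95%. The latter is not the repeated-measures model proposed under the fix, and it did well where stopping depended only on observed 2-hour values. It shows that the earlier OGTTs carry useful information, not that any one model removes the bias.

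**The case against.** The strongest reply is that the protocol does not prescribe an observed-cases analysis. It does not say that earlier OGTTs are ignored, does not rule out imputation and does not tie this outcome to 36 months. Missing-data handling is often left to an analysis plan, which is not shown here. That stands as far as it goes: a reader might infer that the protocol commits to a complete-case regression, and the text does not say so. But the non-collection, the outcome, the intention-to-treat claim and a regression on treatment group alone are all fixed in this document. Followed as written, they do not deliver an intention-to-treat comparison at 36 months.

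Four other limits stand.

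- A reader might infer that only non-converters are compared. That is too strong. Those first diagnosed at the 36-month visit have a value (10.0% and 6.5% above), and every converter has values up to diagnosis.
- A reader might take understatement as certain. It is not. Diagnosed participants go to GP diabetes care, some diagnoses rest on fasting glucose, and step 5 shows the sign can change.
- A reader might expect the loss to worsen as the intervention succeeds. In the second set of simulations, recovery was 69%, 70% and 72% for true differences of 0.51, 1.00 and 1.30 mmol/l. The loss grows in absolute terms, not in proportion.
- A repeated-measures model projects the pre-diagnosis course onto people who have left the intervention and entered GP care. That is a hypothetical quantity and must be described as such.

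**Conclusion.** The point holds for one secondary outcome, at moderate severity. On the planning rates and a constant hazard, about 25.0% of control and 14.5% of intensive-arm participants would lack a 36-month 2-hour value because of the primary outcome itself. A regression on the remaining values should not be called intention to treat.

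The size and direction of the bias are less secure. If converters' glucose stays high, roughly 55–83% of the true difference is recovered, under assumed glucose parameters. If care after diagnosis lowers their glucose, the bias could shrink, vanish or reverse. What is certain is that the comparison has no defined target for participants after diagnosis.

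The documents do not support a wider reading. The rule stops only the OGTT and its 120-minute sample, so HbA1c and fasting glucose can still be collected, and the primary outcome does not depend on values after diagnosis. Where the bias is towards no effect, it would not create a false claim of benefit.

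**What to change.** For 2-hour glucose only, replace the regression on treatment group alone with a likelihood-based repeated-measures model over baseline, 12, 24 and 36 months. It should account for clustering by practice and keep every OGTT value up to and including the diagnostic one. Then:

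- State that the model estimates 2-hour glucose as if the pre-diagnosis course had continued.
- Add a sensitivity analysis for values after diagnosis, for example carrying the diagnostic value forward, and a range of assumed post-diagnosis reductions.
- Do not label an observed-cases 36-month comparison as intention to treat.

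The cost is a little analysis work and one modelling assumption to be stated openly. No new data are needed, and nothing changes in how participants are managed after diagnosis.
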